#### Sample size

In general, 12 to 15 patients per group provided statistical power in MRI studies [21]. According to our previous studies, 25 patients in each group has a more stable statistical power for brain functional network analysis [22]. In order to have a powerful and repeatable statistical power, we require 30 patients per group in this trial. Considering a 20% dropout rate and the possible excessive head motion during scanning, we will include 36 KOA participants in each group. Finally, we plan to enroll 108 participants and each group will undergo two MRI scans to investigate the different central responses among verum acupuncture, sham acupuncture and waiting-list treatment in KOA patients with pain.

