### Outcome measurement

The clinical outcome will measure patients’ knee pain and physical function, quality of life (QOL) and emotional status. All measurement will be performed at the baseline and at the end of the treatment. The primary outcome measurements are the Visual Analog Scale (VAS)[25] and short-form of the McGill Pain Questionnaire (SF-MPQ) [26]. The VAS is a 10-point scale selected to quantitatively evaluate the level of knee pain during the study. It scores from “0 (none),” “about 2 (mild),” “around 5 (moderate),” “almost 8 (severe),” and “nearly 10 (unbearable)” spaced along the continuum. The SF-MPQ focuses on evaluating the sensory and affective components of knee pain in the last 2 weeks. It mainly consists of 15 descriptors (11 sensory and four affective) rating on an intensity scale as “0 = none,” “2 = moderate,” and “3 = severe.” A higher total score indicates more severe pain.

The secondary outcomes are the Western Ontario and McMaster Universities Osteoarthritis Index (WOMAC) [27], the Attention Test Scale (ATS), the Pain Assessment of Sphygmomanometer (PAS) [28] and the 12-Item Short Form Health Survey (SF-12) [29]. The WOMAC is a self-administered questionnaire consisting of 24 items divided into three subscales: pain (five items), stiffness (two items) and physical function (17 items). These measurements will be used to subsidiarily evaluate the symptom and QOL improvement at the baseline and the end of treatment.

Furthermore, to investigate the influence of emotional state on the brain activity, the Self-rating Anxiety Scale (SAS) [30] and the Self-rating Depression Scale (SDS) [31] will be used at the baseline and the end of treatment. To ensure the consistency of acupuncture manipulation, the *deqi* scale will be performed after each acupuncture treatment (Fig. 2). The *deqi* scale is derived from the Chinese version of the modified Massachusetts General Hospital Acupuncture Sensation Scale (C-MASS) [32, 33], the validity and reliability of which have been tested [33, 34]. The scale will be used to evaluate the needle sensations (including soreness, numbness, fullness, heaviness, aching), respectively. All the evaluations are evaluated by two trained, licensed physicians.

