### Data analysis

Before the data analyses, the research group will provide a statistical scheme to the statisticians. The scheme will include the required data and processing method. The data analysis process according to the scheme will be completed by statisticians who are independent from the research team and blinded to the test settings.

For the clinical data, statistical analyses will be performed with SPSS 22.0 statistics software (IBM Corp, Armonk, NY, USA). For the fMRI data, preprocessing and functional connectivity analysis will be performed by SPM12 software (SPM12, Wellcome Department of Imaging Neuroscience, London, UK; http://www.fil.ion.ucl.ac.uk/spm/) performing on MATLAB 8.6 (Mathworks, Inc., Natick, MA, USA) .

Both between and within groups, the numerical variables include the clinical data collected from the VAS, the short form of the McGill Pain Questionnaire, the WOMAC, ATS, SAS, SDS, PAS, *deqi* scale and the SF-12 scale, and Fisher’s transformed z value by functional connectivity analysis on neuroimaging data. Since there are three groups (verum acupuncture group, sham acupuncture group and waiting-list group) with two time points (pre-treatment and post-treatment), the repeated measures analysis of variance (ANOVA) will be employed to analyze both the clinical and neuroimaging data generated by the present study design. In the 2 × 3 group factorial design, the dependent variables were the clinical/neuroimaging data collected from pre-treatment and post-treatment, and data in the three different conditions (groups) will serve as the independent variable. Then, *t* tests will be used in the post-hoc analysis. The chi-square test will be used for categorical variables. All data are presented as the mean ± standard deviation (SD). Data are analyzed following intention to treat. A two-sided test is applied for available data and *P* < 0.05 is considered statistically significant. Finally, the Pearson’s correlation between the changes of cerebral activity and the improvement of clinical variables will be performed in each group.

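### The planned 3 × 2 repeated-measures ANOVA treats baseline as a second outcome and so is less precise than a baseline-adjusted comparison; the intention-to-treat label also needs reconciling with the use of available data

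*Protocol article*

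**What the plan says.** In the protocol article, the Data analysis section states that "the repeated measures analysis of variance (ANOVA) will be employed to analyze both the clinical and neuroimaging data generated by the present study design". The Abstract gives the layout as three groups by two time points. On the role of each variable, Data analysis says that "the dependent variables were the clinical/neuroimaging data collected from pre-treatment and post-treatment" and that "data in the three different conditions (groups) will serve as the independent variable". Baseline therefore enters as a second outcome value, and no covariate is named. For pairwise follow-up, t "tests will be used in the post-hoc analysis", with no mention of baseline adjustment.

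A baseline is available. The Outcome measurement section says: "All measurement will be performed at the baseline and at the end of the treatment". That covers both primary outcomes (VAS and SF-MPQ), the secondary scales and the two mood scales. The *deqi* scale, taken after each treatment, has no pre-treatment value.

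On the analysed set, Data analysis says "Data are analyzed following intention to treat". The next sentence applies the two-sided test to available data. The Sample size section requires 30 patients per group and, "Considering a 20% dropout rate" and possible head motion, enrols 36. It gives no effect size, SD or numerical power. Data analysis also refers to a separate statistical scheme, which is not shown.

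**The concern.** In a randomised trial with one baseline and one follow-up value, the baseline can be used in two ways. Subtracting it, as the group-by-time test in effect does, fixes its coefficient at 1. ANCOVA estimates the coefficient from the data. Unless the true slope of post on pre is 1, subtraction over- or under-corrects and leaves avoidable noise in the treatment contrast.

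This matters here because the arms are small (30 required per group) and the article describes simple randomisation with no stratification, so chance baseline differences are to be expected. The lost precision affects both primary outcomes and could be recovered from data already collected.

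The second issue is labelling. A classical repeated-measures ANOVA uses only patients with both values. If it is run that way and reported as intention to treat, readers would take a complete-pair analysis for one of everyone randomised.

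**Working it through.** **The plan's own figure.** 30 × 1.2 = 36 per group, and 3 × 36 = 108, as stated. (Dividing instead, 30/0.8 = 37.5, gives 38; that is a side remark.) A full 20% loss from 36 leaves 36 × 0.8 = 28.8, about 29, against 30 required. The figure of 30 cannot be reproduced from a power calculation, because no inputs are given.

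**Inputs.** From the article: three arms, one pre and one post value, two-sided 5% level, 30 evaluable per arm. Assumed, because the article gives none: pre-post correlation r of 0.3 to 0.7, and true pairwise differences of 0.5 to 0.8 SD.

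**Step 1: what the group-by-time test is.** With two time points, the interaction F test equals a one-way ANOVA of the change post − pre.

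**Step 2: per-patient variances** (SD s, the same at both visits).
- Change score: 2(1 − r)s²
- ANCOVA: (1 − r²)s²
- Ratio ANCOVA/change: (1 − r²)/[2(1 − r)] = (1 + r)/2

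| r | Ratio | Patients needed by the change-score test relative to ANCOVA |
|---|---|---|
| 0.3 | 0.65 | 1/0.65 = 1.54 |
| 0.5 | 0.75 | 1/0.75 = 1.33 |
| 0.7 | 0.85 | 1/0.85 = 1.18 |

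The direction does not depend on equal variances. If the post SD is k times the pre SD, with the pre variance set to 1, then (1 + k² − 2rk) − k²(1 − r²) = (1 − rk)², which is never negative. Only the size of the ratio depends on k.

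**Step 3: a comparison that needs no assumed effect size.** Suppose the group-by-time contrast had exactly 80% power at 30 per arm. ANCOVA would then have 93.5%, 89.9% or 86.0% power at r = 0.3, 0.5 or 0.7. Equivalently, it would reach 80% with 20, 23 or 26 per arm (30 × 0.65 = 19.5, 30 × 0.75 = 22.5, 30 × 0.85 = 25.5, rounded up).

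**Step 4: an illustration at an assumed 0.7 SD difference, 30 per arm.** Power = Φ[δ/(SD × √(2/n)) − 1.96]. At r = 0.5:
- Change: SD = 1, and 0.7/√(2/30) = 2.711, so Φ(0.751) = 77%.
- ANCOVA: SD = √0.75 = 0.866, and 0.7/(0.866 × 0.2582) = 3.130, so Φ(1.170) = 88%.

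| r | Change contrast | ANCOVA contrast | Simulated three-arm F test: change | Simulated three-arm F test: ANCOVA |
|---|---|---|---|---|
| 0.3 | 63% | 81% | 51% | 69% |
| 0.5 | 77% | 88% | 66% | 78% |
| 0.7 | 94% | 97% | 89% | 93% |

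The simulation (3,000 runs, effects of 0, 0.35 and 0.7 SD) includes ANCOVA's cost of estimating the slope.

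**Step 5: how far the level of power depends on the assumptions.** At 30 per arm the planned contrast has 37% power (0.5 SD, r = 0.3) to 98% (0.8 SD, r = 0.7).

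**Step 6: the analysed set.** Intention to treat means everyone randomised, in the assigned arm. Available data, under a classical repeated-measures ANOVA, means patients with both values. The two coincide only if nothing is missing, and the sample size makes an allowance for loss.

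**The case against.** The strongest reply is that the planned test is valid. With randomisation, the group-by-time comparison is unbiased, so preferring ANCOVA is an efficiency recommendation and not the correction of an error. That stands. So does the point that the gain is small when r is high: at r = 0.7 and 0.7 SD, power goes from 94% to 97%.

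A reader might infer more than the article supports in three places.

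- *That the trial is underpowered.* Less efficient is not the same as underpowered. With no stated power, effect size or SD there is nothing to fall short of, and step 5 shows how widely the answer moves with the assumptions.
- *That the test is the group main effect*, because only group is called the independent variable. That test would average in the untreated baseline and halve the effect. But the Abstract's three-by-two layout, and the two time points and factorial design in Data analysis, plainly make time the second factor. The interaction is not named as the test, but that is a gap in wording.
- *That about 7 of 36 patients per arm (36 × 0.2 = 7.2) will be deleted.* The 20% is a planning allowance. No SPSS procedure is named, and missing-data handling may be set in the scheme that is not shown. The Trial status figures (89 recruited, 80 having completed the intervention) are not a dropout rate, since recruitment was continuing. Most of the allowance is already covered by the sample size (about 29 left against 30). No loss by arm is given, so bias from differential loss is a possibility only.

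It is also fair to say that ANCOVA does not by itself repair the intention-to-treat claim. On observed post-treatment values it omits the same patients. In a mixed model with a single follow-up, a patient with baseline only adds almost nothing to the treatment contrast.

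**Conclusion.** The point holds as one of precision and labelling. The planned group-by-time test is a change-score analysis. Its contrast variance exceeds that of ANCOVA by the factor 2/(1 + r): 1.54, 1.33 or 1.18 at r = 0.3, 0.5 or 0.7. These sizes rest on an assumed r and on equal pre and post variances; the direction needs neither. The method is not invalid, and no power deficit is established.

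On the analysed set, what remains is that the article's two statements, intention to treat and available data, have to be reconciled. The documents do not show that patients will be dropped or that the result will be biased.

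**What to change.** - **Clinical outcomes.** For VAS, SF-MPQ and the other scales measured at both visits, compare post-treatment values between arms by ANCOVA with the same scale's baseline as covariate, or by a baseline-constrained mixed model.
- **Contrasts.** Name verum versus sham and verum versus waiting list as the baseline-adjusted contrasts, in place of unadjusted post-hoc t tests.
- **Imaging.** Where feasible, use the baseline connectivity value as a covariate in the imaging model too.
- **Analysed set.** Keep patients with unusable scans in the clinical analysis, in their assigned arm. Do not call an analysis limited to patients with both values, or to evaluable scans, intention to treat; describe each by what it contains.

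For the clinical outcomes the cost is a change of wording, with no new data or patients; recruitment was still open when the article was written. The imaging model may take more work in the planned software, hence the qualification. ANCOVA assumes a linear baseline effect. A mixed model or imputation, if used, also assumes that values are missing at random.

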KOA is a complex, chronic pain condition partly due to both nociceptive and neuropathic mechanisms [13]. Previous studies have demonstrated that central sensitization, a pathological change in the central nervous system, plays an important role in the pathogenesis of KOA [14, 15]. With the widely application of neuroimaging techniques in pain research, investigators not only mapped the brain regions which are involved in the central pathogenesis of chronic pain, but also partly explored the central mechanism of acupuncture-induced analgesia by detecting the cerebral responses elicited by acupuncture. Using resting-state functional magnetic resonance imaging (rs-fMRI), researchers found that the patients with chronic pain demonstrated altered functional connectivity (FC) of the medial prefrontal default-mode network (DMN) and a changed regional homogeneity (ReHo) value of the anterior cingulate cortex (ACC) [16–18]. These results greatly enhanced the understanding of the central mechanism of chronic pain and have provided an approach to investigating the mechanism of acupuncture-induced analgesia. For instance, a functional magnetic resonance imaging (fMRI) study has shown that acupuncture can regulate the descending pain-modulatory system of KOA patients by enhancing the FC between the right frontoparietal network (rFPN) and the medial prefrontal cortex (mPFC) [19]. However, the sample size (only 10 in each group) and the dosage of acupuncture treatment (six acupuncture treatments for 4 weeks) of that study were relatively small, and the self-healing tendency of KOA patients could not be excluded due to the lack of waiting-list control.

So, this study aims to (1) investigate the influence of verum acupuncture treatment on the brain activities of patients with KOA compared with that of sham acupuncture treatment and waiting list patients by using fMRI with a larger sample size (36 patients in each group) and (2) analyze the possible correlations between the changes of cerebral activity and the improvement of clinical variables in each group, so as to explore how acupuncture manages pain by modulating brain function.

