#### Randomization

Eligible patients will be randomized in a ratio of 1:1:1 to the verum acupuncture group, sham acupuncture group and waiting-list group with 36 patients in each group using simple randomization. Random number lists will be created in accordance with PROC PLAN of SAS 9.2 (SAS Institute Inc., Cary, NC, USA). The randomization allocation will use sequentially numbered, opaque and sealed envelopes by an independent assistant.

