### Limitations

It is difficult to blind patients in the waiting group and acupuncturists for no acupuncture intervention will be performed on this group during the study. However, researchers, acupuncturists and outcome assessors are separate and the group allocation will be concealed.

In summary, this fMRI trial is designed to investigate the central mechanism of verum acupuncture in the treatment of KOA by comparing that of sham acupuncture and waiting-list groups, and by analyzing the correlation between the cerebral activity changes and clinical variable changes. We expect that our findings can provide visualization reference for the clinical application of verum acupuncture for KOA management.

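### Aim 2 tests the brain-symptom correlation separately in each group and never compares the groups, so significance in one arm and not in another cannot support a mechanism specific to verum acupuncture

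*Protocol article*

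**What the plan says.** In the protocol article, the Background gives aim 2 as to "analyze the possible correlations between the changes of cerebral activity and the improvement of clinical variables in each group", and its purpose as "so as to explore how acupuncture manages pain by modulating brain function". The last sentence of Data analysis carries this out literally: Pearson's "correlation between the changes of cerebral activity and the improvement of clinical variables will be performed in each group". The general testing rule there is "A two-sided test is applied for available data", with P "< 0.05 is considered statistically significant".

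The final paragraph under Limitations says that the central mechanism of verum acupuncture will be investigated by comparison with the sham and waiting-list groups and "by analyzing the correlation between the cerebral activity changes and clinical variable changes".

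The only between-group analysis named for numerical variables is the repeated-measures ANOVA (three groups, two time points) with post-hoc t tests. It compares mean changes. It does not ask whether the relation between brain change and symptom change differs between groups.

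**The concern.** The sham and waiting-list arms are there so that an effect can be attributed to verum acupuncture. The Background criticises an earlier imaging study because, without a waiting list, it could not exclude spontaneous improvement. For aim 2 the plan makes no use of these controls. Each arm's correlation is set against zero, and the three results stand side by side.

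If the verum correlation is significant and the sham correlation is not, the natural reading is that the brain-symptom link belongs to verum. Separate tests against zero do not support that reading. The two estimates may be close together, and the arms may share the same true correlation. At about 30 patients per arm, sampling error alone produces such a split quite often over a plausible range of correlations.

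**Working it through.** **Inputs**
- Enrolled per group: 36; evaluable target 30; dropout 20% (Sample size).
- Allocation: "Eligible patients will be randomized in a ratio of 1:1:1".
- Test: two-sided, 0.05 (Data analysis).
- True correlation ρ: not given. Assumed equal in verum and sham, and varied from 0 to 0.7.

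**The plan's own figure.** 30 × 1.2 = 36 per group, which reproduces the stated enrolment. Read the other way, a 20% loss from 36 leaves 36 × 0.8 = 28.8, about 29. The article's own target is 30. Both are used below, and the choice hardly matters.

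**Significance threshold for r.** With n = 29 there are 27 degrees of freedom and t(0.975) = 2.052. The critical |r| = t / √(27 + t²) = 2.052 / √(27 + 4.211) = 0.367. At n = 30 it is 0.361.

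**Chance that the two arms split when they do not differ.** By Fisher's z, power per arm is p = Φ(atanh(ρ)·√(n − 3) − 1.96) + Φ(−atanh(ρ)·√(n − 3) − 1.96). Simulation with 40,000 runs per cell agreed within 2 percentage points. With the same ρ in two independent arms, P(exactly one significant) = 2p(1 − p). By symmetry, half of this is verum significant and sham not.

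Example at n = 29, ρ = 0.36: atanh(0.36) = 0.377; 0.377 × √26 = 1.922; p = 0.485; 2 × 0.485 × 0.515 = 0.50.

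| True ρ in both arms | p, n = 29 | Exactly one significant, n = 29 | Verum only, n = 29 | Exactly one significant, n = 30 |
|---|---|---|---|---|
| 0 | 5% | 10% | 5% | 10% |
| 0.2 | 18% | 29% | 15% | 30% |
| 0.3 | 35% | 46% | 23% | 46% |
| 0.36 | 49% | 50% | 25% | 50% |
| 0.4 | 58% | 49% | 24% | 48% |
| 0.5 | 80% | 32% | 16% | 30% |
| 0.6 | 94% | 11% | 5% | 10% |
| 0.7 | 99% | 1% | 1% | 1% |

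At n = 29 the split is at least 40% only for ρ between about 0.26 and 0.46. With no losses (n = 36) it is 49% at ρ = 0.3 and 21% at ρ = 0.5.

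**What a direct comparison would say.** The difference of two Fisher z values has SE = √(2/(n − 3)) = √(2/26) = 0.277. Take observed r = 0.45 in one arm (P = 0.014) and r = 0.25 in the other (P = 0.19). The difference is 0.485 − 0.255 = 0.229; 0.229 / 0.277 = 0.83; P = 0.41. One arm is significant and the other is not, yet there is no evidence that they differ.

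**Power of the direct comparison at 29 per arm (two-sided 0.05).**
- 0.4 versus 0: 33%
- 0.5 versus 0: atanh(0.5) / 0.277 = 0.549 / 0.277 = 1.98, so 51%
- 0.6 versus 0: 71%
- 0.5 versus 0.2: 24%
- For 80%: a gap of (1.96 + 0.84) × 0.277 = 0.777 in z, that is about 0.65 versus 0

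**The case against.** The strongest reply is that the analysis matches the aim. Aim 2 asks for correlations within each group and uses the language of exploration, and nowhere does the article say that a mechanism will be declared because one arm is significant and another is not. That is right. A reader might infer such a decision rule from the Background, Data analysis and Limitations taken together, but it is not stated. What remains is that the article uses these correlations for a verum-specific mechanism and names no analysis that could support that use.

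A second reply is that the mechanism does not require different correlations. Acupuncture could relieve pain through connectivity with the same brain-symptom relation in every arm, while verum simply changes connectivity more. That difference in change belongs to aim 1 and is tested by the ANOVA. This also stands. It limits what a null comparison would mean, but it does not license reading separate P values as a contrast.

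Third, it is tempting to say that at 29 per arm the result is a coin toss. The document does not support that. The figure depends on an unknown common correlation: over the range 0 to 0.7 the split runs from 1% to 50%, and the verum-only pattern never exceeds 25%.

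Finally, a reader might infer that multiplicity and covariates are ignored. Data analysis refers to a statistical scheme, not shown here, that will set out the processing method. Those details may be in it and are not part of this point.

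**Conclusion.** The point holds in a limited form. The within-group method is fixed in two places, and no between-group comparison of the correlations is named, although the mechanism statement for verum acupuncture draws on both the correlations and the control groups. If verum and sham share the same true correlation, they split on significance in 29% to 50% of trials for a correlation between 0.2 and 0.4, in about 10% at 0 or 0.6, and in 1% at 0.7; half of these splits are verum only. These figures rest on an assumed equal correlation, independent arms and 29 evaluable patients per arm, and they are nearly the same at 30. They show how weak a significant-versus-not reading would be. They do not show that the investigators intend to make it.

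**What to change.** In Data analysis, and in the statistical scheme that goes to the statisticians:

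1. Add a direct verum-versus-sham comparison of the brain-symptom relation. One option is a single model over all groups: post-treatment clinical score on baseline score, connectivity change, group, and group × connectivity change, with the verum-sham contrast of the last term as the test. The other is a Fisher z difference between the two correlations. Choose one beforehand: the first compares slopes and the second compares correlations, and the power figures above belong to the second.
2. Name the clinical score and the connectivity measure to which the comparison applies. The article names no single connection.
3. Report per-group r with 95% CI as description.
4. State that no arm-specific mechanism claim will be made without the direct comparison, and label aim 2 exploratory.

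No new data are needed. Trial status reports recruitment still open, and the scheme is to be supplied before analysis, so a change of wording is enough. The cost is fewer arm-specific claims and a comparison with low power (about 51% for 0.5 versus 0 at 29 per arm). The report should therefore say that a null result neither shows that the relation is equal nor refutes the mechanism.
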